## Clinical Chemistry and Hematology

The blood samples for serum hematology and chemistry tests will be collected before study drug intake as specified in Section 2; tests may be performed more often if clinically indicated. At the Day 1 visit, blood samples should be collected before the first dose of study drug. The baseline laboratory test results for clinical assessment for a particular test will be defined as the last measurement before the initial dose of study drug.

Additional hematology and chemistry laboratory assessments will be performed based on the clinical indications per institutional guidelines and regional standards. Chemistry and hematology lab results obtained within 48 hours prior to the first dose must be reviewed by the treating investigator prior to administration of that first dose. For other time points, tests may be completed ≤ 3 days before the scheduled visit and must be reviewed before dosing.

For chemistry labs performed for TLS prophylaxis and monitoring during Cycle 1, refer to Section 3.14, and Protocol Appendix F for specific requirements.

### Tumor Lysis Syndrome Chemistry Panel

Samples for TLS chemistry will be taken at the time points specified in Table 8, while subjects are hospitalized for the first 2 doses of ABBV-467. Samples should also be obtained as clinically indicated in the opinion of the investigator.

**Table 8. TLS Chemistry Panel Sampling Times**

| Cycle 1 Day 1                                                            | Cycle 1 Day 8                                                            | Cycle 1 Days 15 & 22 |
|--------------------------------------------------------------------------|--------------------------------------------------------------------------|----------------------|
| 0 (pre-infusion)
6 – 8 hours post EOI
24 hours post-EOI (on Day 2) | 0 (pre-infusion)
6 – 8 hours post EOI
24 hours post-EOI (on Day 9) | 0 (pre-infusion)     |

EOI = end of infusion

### Creatine Phosphokinase and Troponin Enzymes

Blood samples will be collected on the days specified in Section 2 for analysis of creatine phosphokinase and troponin serum concentrations. Clinical significance of these enzymes will be evaluated within the context of the study. The sampling times are listed in Table 9. Samples should also be obtained as clinically indicated in the opinion of the investigator.

**Table 9. Creatine Phosphokinase and Troponin Sampling Times**

| Cycle 1                                             |                                                    | Cycles 2 - 8 | Cycles 2, 4, 6, 8 |
|-----------------------------------------------------|----------------------------------------------------|--------------|-------------------|
| Days 1 – 3                                          | Days 15 – 17                                       | Day 1        | Day 15            |
| 0 (pre-infusion)
4, 8, 24, and 48 hours post-EOI | 0 (pre-infusion)
4, 8, 24 and 48 hours post-EOI | EOI          | EOI               |

EOI = end of infusion

Note: All samples will be shipped to central lab for processing. Sample times are relative to ABBV-467 infusion.

### Pregnancy Tests (Serum and Urine)

Women of childbearing potential must have a negative pregnancy test before initiating therapy. A pregnant or breastfeeding female will not be eligible for participation or continuation in this study. Pregnancy testing should not be performed for postmenopausal women; determination of postmenopausal status will be made during the screening period based on the subject's history.

A qualitative serum pregnancy test will be performed at Screening and a urine pregnancy test will be performed at baseline (or upon confinement in each period) for all female subjects of childbearing potential.

If the serum pregnancy test is positive the subject is considered a screen failure. If the serum pregnancy test is borderline, it should be repeated 2 days later to determine eligibility.

If the repeat serum pregnancy test is:

- Positive, the subject is considered a screen failure;
- Negative, the subject can be enrolled into the trial;
- Still borderline, the AbbVie TA MD will be consulted.

Additional urine pregnancy tests will be performed at visits indicated in the Activities Schedule and Section 2. More frequent pregnancy tests can be performed throughout the study at the investigator's discretion or if required per local/country requirements. Urine pregnancy test must be obtained at Cycle 1 Day 1, if it has been > 7 days since obtaining the serum pregnancy results at screening.

A pregnancy test should be repeated on Day 1 of each cycle, evaluated prior to dosing, and at Final Visit.

If the urine pregnancy test (which is performed at the site) is negative, begin or continue dosing. If urine pregnancy test is positive subjects must discontinue from the study.

### Coagulation

Prothrombin time (PT) or international normalized ratio (INR) and activated partial thromboplastin time (aPTT) samples will be collected at visits indicated in Section 2. Coagulation panel should be repeated on Day 1 of each cycle for subjects taking vitamin K antagonists or if otherwise clinically indicated.

### Urinalysis

Urinalysis tests will be performed as specified in Section 2. Dipstick urinalysis will be completed by the local laboratory at all required visits. Specified abnormal macroscopic urinalyses defined as leukocytes, nitrite, protein, ketones, or blood greater than negative, or glucose greater than normal should be followed up with a microscopic analysis (red blood cells, white blood cells, epithelial cells, bacteria, yeast, parasites, casts, and crystals) at the local laboratory. Urinalysis data may be collected if associated with an AE.

## 3.16 Disease Assessments

---

### Multiple Myeloma Assessments

Disease assessments will be performed at the visits indicated in Section 2. MM subjects will be evaluated using the adapted International Myeloma Working Group (IMWG) 2016 criteria (see Section 7.3). Note that serum and urine for IMWG assessments do not need to be collected at C1D1 if the Screening samples were collected within 7 days of C1D1.

All subject's IMWG laboratory assessments (serum protein electrophoresis [SPEP], urine protein electrophoresis [UPEP], serum and urine immunofixation, serum free light chains, and serum quantitative immunoglobulins) will be performed by central laboratory, however, local labs may be performed at the investigator's discretion. All local laboratory results must be entered into the eCRF. Imaging and bone marrow assessments will be performed locally. Disease status should continue to be collected for MM subjects after study drug discontinuation for reasons other than disease progression.

## Serum Protein Electrophoresis, Serum Protein Immunofixation, Serum Quantitative Immunoglobulins

Peripheral blood samples for SPEP, serum protein immunofixation, and serum quantitative immunoglobulin testing will be collected as outlined in Section 2. Serum protein electrophoresis and serum immunofixation will be collected for all subjects at baseline and throughout the study until progressive disease or withdrawal of consent, regardless of SPEP being measurable or M-protein presence at baseline.

The assessment of SPEP M-protein and serum immunofixation at the time of possible VGPR or CR/sCR is mandatory, even in subjects without measurable values at baseline.

## Serum Free Light Chains

Blood samples for serum free light chain (FLC) testing will be collected for all subjects as outlined in Section 2.

Subjects with measurable disease in either SPEP and/or UPEP will be assessed for response only based on these 2 tests and not by the FLC assay. FLC response criteria are only applicable to fulfill the requirements of sCR or CR per IMWG criteria.

## Urine Protein Immunofixation and Urine Protein Electrophoresis, 24-Hour Urine

Urine samples (24-hour) for urine protein immunofixation and UPEP for M protein testing will be collected for all subjects as outlined in Section 2. Urine protein electrophoresis and urine immunofixation will be collected for all subjects at baseline and throughout the study until progressive disease or withdrawal of consent, regardless of UPEP being measurable or M-protein presence at baseline.

The assessment of UPEP M-protein and urine immunofixation at the time of possible VGPR or CR/sCR is mandatory, even in subjects without measurable values at baseline.

Subjects with measurable disease at baseline by SPEP and UPEP must be followed by both SPEP and UPEP assessment of M-protein for response assessment.

## Skeletal Survey

Whole body skeletal imaging will be done at screening using either conventional radiography, low-dose whole body computed tomography (CT), positive emission tomography CT component only (PET-CT), or whole-body magnetic resonance imaging (MRI). The methodology used at baseline should be used at all the follow-up time points for consistent evaluation of any lesions identified. Historical skeletal survey results obtained within 30 days before the first dose may be used for screening (using the above techniques). A skeletal survey will be comprised of the following:

- lateral radiograph of skull.
- antero-posterior and lateral views of the spine.
- antero-posterior views of pelvis, ribs, femora, tibiae, fibulae, humeri, ulnae, and radii.

Skeletal surveys should be completed as outlined in Section 2. After the screening procedure, skeletal survey should only be performed if clinically indicated. While the subject is on study, survey (if done) should record any changes to the number of or size of lytic lesions as well as the number and location of any new skeletal or lytic lesions. Changes in measurable lesions over the course of therapy will be assessed using IMWG criteria may be performed at any time during the study if clinically indicated per the investigator.

### Plasmacytoma Evaluation

CT, MRI, or PET-CT scans should be performed at baseline, if clinically indicated, to assess for presence of extramedullary plasmacytoma. Plasmacytoma evaluation should be performed to confirm PR/CR or progressive disease, or otherwise as clinically indicated, every 12 - 16 weeks. The same radiological method should be used throughout the study.

### Bone Marrow Aspirate and Biopsy

Bone marrow aspirate and biopsy should be completed as outlined in Section 2. Bone marrow aspirates and biopsies performed as standard of care throughout the study should also be captured on an eCRF.

A sufficient bone marrow aspirate or biopsy must be collected for clinical assessment (pathology, plasma cell % and kappa ( $\kappa$ )/lambda ( $\lambda$ ) for clonality per IMWG criteria) and cytogenetics performed by a local laboratory as well as for shipment of a portion for the biomarker analyses (refer to Section 3.8). Bone marrow biopsy and aspirate specimens for biomarker analyses are to be split from those collected for locally performed IMWG disease assessments; adequate samples should be obtained to allow for biomarker analysis.

A bone marrow aspirate collection is mandatory at screening, to confirm sCR/CR (including MRD assessments), at 12, 18, and 24 months post confirmation of sCR/CR, and at the Final Visit. Additionally, should an aspirate be performed at any time to confirm a CR or when one is suspected, then an aliquot for biomarker studies should be provided.

Bone marrow core biopsy (fixed formalin paraffin embedded [FFPE] core) should be also collected, unless not recommended per institutional guidelines. However, a bone marrow biopsy is mandatory in the circumstance that an aspirate sample is not available (e.g., due to a dry tap). Fresh biopsies are preferred but archived tissue is acceptable if representative of current disease. Core block or tissue slides are acceptable. Bone marrow core biopsies are optional to confirm sCR/CR, or at the Final Visit.

De-identified copies of all bone marrow biopsy and aspirate reports must be provided to the sponsor and may be submitted for central review to confirm response.

### Acute Myeloid Leukemia Assessments

Assessments of AML disease status by the modified International Working Group (IWG) criteria (see Section 7.4) will be performed at the visits indicated in Section 2.

All AML subjects will have response assessment according to the modified IWG criteria for AML. Progressive disease is defined per European LeukemiaNet recommendations. If additional treatments are needed to optimize subjects' medical care, they can be performed following institutional standards and procedures. Subject's disease assessment is based on the most recent physical examination, bone

marrow results and recent hematology values. For subjects who require a delay in next cycle of study treatment for blood count recovery after a bone marrow evaluation, hematology values for up to 2 weeks or pre-dose labs from Day 1 of the next cycle can be used to determine the IWG response.

All AML subjects who completed at least 1 cycle of study treatment will be assessed by the investigators using the modified IWG criteria for AML as described in Section 7.4. Subjects who have discontinued study treatment prior to completion of Cycle 1 will be deemed non-evaluable for response assessment. In addition to the response assessment using the above response criteria, each subject will also be evaluated for complete response with partial hematologic recovery (CRh) based on the hematologic parameters.

Bone marrow aspirate and biopsy should be completed as outlined in Section 2. Bone marrow aspirates and biopsies performed as standard of care throughout the study should also be captured on an eCRF.

A bone marrow aspirate and biopsy must be performed for all subjects during screening to collect mandatory samples for disease and biomarker assessments. Bone marrow aspirate and biopsy will also be collected anytime that progressive disease is suspected.

Bone marrow biopsy materials (i.e., block or slides) are to be submitted from screening and final visits, and aspirate is to be provided from screening, C2D1, Day 1 of every 3 Cycles thereafter (i.e., C5D1, C8D1, C11D1, etc.), and the Final Visit. Additionally, should an aspirate be performed at any time to confirm a CR or when one is suspected, then an aliquot for biomarker studies should be provided.

Bone marrow aspirate and biopsy samples must be collected for all subjects for each of the disease assessments. Bone marrow core biopsy sample collection is considered an optional procedure only for subjects enrolled at sites in countries where an aspirate evaluation by morphologic assessment and flow cytometry is considered standard of care. For these subjects if the aspirate sample is inadequate or unevaluable for disease assessment, repeat bone marrow aspirate and biopsy must be performed within 7 days. A corresponding local laboratory pathology report should be sent to the central laboratory for each local disease assessment which is conducted.

The C2D1 bone marrow aspirate and biopsy should be performed within  $\pm 3$  days of Cycle 1 Day 28 and reviewed prior to the administration of study drugs for Cycle 2, if possible. For subjects who require a delay in study treatment for blood count recovery after a bone marrow evaluation, local or central laboratory values obtained up to 2 weeks after C2D1 (i.e., C2D15) can be used to determine the response. Subsequent response assessment should be conducted after every 3 cycles ( $\pm 1$  week; after C4, C7, etc.) and upon any clinical suspicion of relapse. Although AML response assessments should be completed as soon as possible at the end of relevant cycles, the subsequent cycle does not have to be delayed for bone marrow aspirate/biopsy results that are not yet available. For subjects with resistant disease after the first cycle, and who are remaining on study, a repeat bone marrow aspirate/biopsy should be performed after the second cycle in order to confirm and/or clarify response.

Bone marrow biopsy and aspirate specimens for biomarker analyses are to be split from those collected for locally performed disease assessment; adequate samples should be obtained to allow for biomarker analysis. De-identified copies of all bone marrow biopsy and aspirate reports must be provided to the sponsor and may be submitted for central review to confirm response.

Disease status should continue to be collected for AML subjects after study drug discontinuation for reasons other than disease progression.

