### 7.2 Definition for Analysis Populations

---

Efficacy and safety analyses will be performed on the all-treated population which comprises all subjects who receive at least 1 dose of study drug. The PK population is defined as subjects who received at least 1 dose of study drug and have at least 1 valid post-baseline PK data; PK analyses will be based on the PK population.

Details on the analysis population definitions will be provided in the SAP.

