### 7.3 Statistical Analyses for Efficacy

---

Efficacy analysis will be performed separately for subjects with R/R MM and R/R AML.

Efficacy for R/R MM subjects will include analyses of ORR (PR + VGPR + CR + sCR), DOR, and CBR.

Efficacy for R/R AML subjects will include analyses of CRc rate (CR + CRi), CRh, ORR (CRc + PR), and DOR.

Exploratory efficacy analysis includes overall survival (OS) for both R/R MM and R/R AML.

For Parts A and C, efficacy data will be listed for each dose level.

For Parts B and D, efficacy analyses will be performed by cohort for the all-treated population. For binary endpoints (such as ORR, CBR, CRc, CRh), the estimated proportion and the associated 2-sided 90% Clopper-Pearson (exact) confidence intervals (CIs) will be provided for each cohort. DOR will be defined as the time between date of first response and the first occurrence of progression or death from any cause, whichever occurs first. Only responders will be included in the analysis of DOR. DOR for subjects without DOR events at the time of analysis will be censored at the date of last disease assessment. If a subject receives a new anti-cancer therapy, DOR will be censored at the date of last disease assessment prior to the start of the new therapy. DOR will be summarized using the Kaplan-Meier method. The median DOR and its associated 2-sided 90% CIs will be provided for each cohort. For R/R MM subjects, DOR will be analyzed among subjects who achieved PR, VGPR, CR or sCR. For R/R AML subjects, DOR will be analyzed among subjects who achieved CRc or PR. OS will be defined as the time from the date of the first dose of study treatment to the date of death. For subjects who are not deceased, the data will be censored at the last known alive date. OS will be summarized using the Kaplan-Meier method. The median OS and its associated 2-sided 90% CIs will be provided.

Additional details on the efficacy analyses are provided in the SAP.

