## 7.7 Sample Size Determination

---

A total of approximately 108 subjects will be enrolled in this study. In the dose-escalation component, the number of subjects will depend upon the occurrences of DLT events as specified in the allocation rules for BOIN design. Including a minimum of 6 subjects treated during dose escalation at what is ultimately declared the RP2D, it is estimated that approximately 30 subjects each will be treated in Part A and Part C (approximately 60 total).

The expansion component will target enrollment of 20 response-evaluable subjects (with a maximum of 24 subjects enrolled regardless of response evaluability) each into Parts B and D (up to 48 enrolled total) to further evaluate the safety profile, and preliminarily evaluate efficacy, of ABBV-467 at RP2D. Subjects will be considered response-evaluable if they have received at least 1 dose of ABBV-467 and have died, or exited the study due to progressive disease, or had at least 1 post-baseline response assessment per the indication-specific response criteria. Subjects who die or exit for progressive disease, prior to their first baseline assessment, will be considered to have not responded to the therapy.

With a sample size of 24 subjects, the probability to observe at least 1 occurrence of AE is  $\geq 92\%$  if the true incidence of the respective AE rate is  $\geq 10\%$ .

No formal hypothesis testing is planned for this first-in-human study; preliminary assessment of efficacy is a secondary objective of this study. [Table 5](#) provides the lower bound of a one-sided 80% CI corresponding to various observed response rates assuming a total of 20 response-evaluable subjects in each cohort. For example, if a 25% response rate is observed, the lower bound of a one-sided exact CI will exclude 15% (or lower) rates of response, providing some preliminary assessment of efficacy.

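### Operations Manual 3.16 and Section 7.7 classify AML subjects lost during Cycle 1 in opposite ways for response evaluability

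*Protocol*

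**What the plan says.** Operations Manual 3.16, under the AML assessments, contains two linked sentences. The first says who is assessed: "All AML subjects who completed at least 1 cycle of study treatment will be assessed by the investigators using the modified IWG criteria". The second deals with the rest: "Subjects who have discontinued study treatment prior to completion of Cycle 1 will be deemed non-evaluable for response assessment". The reason for stopping plays no part in either.

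Protocol Section 7.7 has its own definition. A subject is response-evaluable if they "received at least 1 dose of ABBV-467 and have died, or exited the study due to progressive disease", or if they had one or more response assessments after baseline. Completing Cycle 1 is not required. The section adds: "Subjects who die or exit for progressive disease, prior to their first baseline assessment, will be considered to have not responded to the therapy". It sets the size of each expansion cohort in the same terms, with a "target enrollment of 20 response-evaluable subjects (with a maximum of 24 subjects enrolled regardless of response evaluability". The note to Table 5 says its cohort size is the number of response-evaluable subjects.

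The analysis population is stated elsewhere. Section 7.2: "Efficacy and safety analyses will be performed on the all-treated population which comprises all subjects who receive at least 1 dose of study drug". Section 7.3, for Parts B and D: "efficacy analyses will be performed by cohort for the all-treated population", with binary endpoints reported as a proportion and the "associated 2-sided 90% Clopper-Pearson (exact) confidence intervals (CIs").

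**The concern.** An AML subject who dies on Day 20 is an evaluable non-responder under Section 7.7 and non-evaluable under the manual. The manual cannot be set aside as informal guidance: it is Appendix J of the protocol, and Section 8.2 requires the study to be conducted in accordance with it.

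Such losses are foreseeable. Section 4.2 describes survival in this AML population in terms of months or weeks, so deaths and progression within the first 28 days are to be expected, and they are treatment failures. A definition that removes them removes non-responders and no responders.

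Two uses of evaluability are exposed: the count that decides when Part D has reached 20, and any response rate or Table 5 reading built on that count. If the conflict is settled only after outcomes are known, the denominator becomes a matter of choice.

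**Working it through.** **Step 1. Apply each rule to the same subject.** Take an AML subject in Part D who receives at least one dose and stops treatment during Cycle 1.

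| Course | Section 7.7 | Manual 3.16 | All-treated (7.2, 7.3) |
|---|---|---|---|
| Dies | evaluable, non-responder | non-evaluable | in denominator |
| Exits for progression | evaluable, non-responder | non-evaluable | in denominator |
| Other reason, response assessed at Final Visit | evaluable | non-evaluable | in denominator |
| Other reason, alive, never assessed | non-evaluable | non-evaluable | in denominator |

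The rules differ in the first three rows and agree in the fourth. The third row can occur, because Appendix D schedules an AML marrow and response assessment at the Final Visit. The manual's response table does not settle the first row: resistant disease requires survival for at least 7 days after Cycle 1 treatment, so a death during Cycle 1 has no failure category there.

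**Step 2. Reproduce the plan's own figures.** The exact one-sided 80% lower bound for x responders among n is the 20th percentile of Beta(x, n − x + 1). With n = 20:

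| x | Computed | Table 5 |
|---|---|---|
| 5 | 0.1584 | 0.158 |
| 6 | 0.2013 | 0.201 |
| 7 | 0.2454 | 0.245 |
| 8 | 0.2906 | 0.291 |
| 10 | 0.3840 | 0.384 |

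All five rows match.

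**Step 3. Size of the difference.** The protocol gives no rate of Cycle 1 loss, so the number is assumed and varied. Take 24 treated (the cap), 5 responders, and k Cycle 1 losses, all deaths or progression exits. All-treated gives 5/24. The manual's rule gives 5/(24 − k). The two-sided 90% limits are the 5th percentile of Beta(x, n − x + 1) and the 95th percentile of Beta(x + 1, n − x).

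| Rule | x/n | Rate | One-sided 80% lower bound | Two-sided 90% CI |
|---|---|---|---|---|
| All-treated | 5/24 | 20.8% | 0.131 | 0.086–0.389 |
| Manual, k = 2 | 5/22 | 22.7% | 0.144 | 0.094–0.420 |
| Manual, k = 4 | 5/20 | 25.0% | 0.158 | 0.104–0.456 |
| Manual, k = 6 | 5/18 | 27.8% | 0.177 | 0.116–0.498 |

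**Step 4. Effect on the count toward 20.** Suppose 20 subjects are evaluable under Section 7.7, 4 of them Cycle 1 deaths or progression exits. Section 7.7 regards the target as met. The manual counts 20 − 4 = 16 and leaves room to enrol up to 24 − 20 = 4 more. If a rate were taken at that point with 5 responders, it would be 5/20 = 25.0% (lower bound 0.158) under Section 7.7 and 5/16 = 31.3% (0.199) under the manual.

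**The case against.** The strongest reply is that the analysis set is already fixed. Section 7.3 puts the Part D efficacy analyses, including CRc and ORR, on the all-treated population. The manual's sentence sits among site procedures and defines no analysis set, so a treated subject it calls non-evaluable stays in the denominator. This stands. A reader might infer that early deaths and failures drop out of the reported AML response rate; the protocol does not say that, and it happens only if the manual's definition is carried into the rate.

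A reader might also infer from Step 3 that the exclusion moves the result across a 15% benchmark. That does not hold up either. Section 7.7 gives 15% as an example after stating that no formal hypothesis testing is planned. The crossing needs about four losses, all deaths or progression exits; with two, the bound is 0.144. It also uses the one-sided 80% planning interval. Under the two-sided 90% interval of Section 7.3, the lower limits of 0.086 and 0.104 both lie below 15%.

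A third tempting reading is that the Section 7.7 safeguard protects nobody, because a baseline assessment precedes dosing. Read literally, that sentence does fail. But the slip for post-baseline is evident, and the sentence before it independently makes treated subjects who die or exit for progression evaluable.

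Finally, replacement of early failures is bounded. The cap of 24 applies whatever the evaluability, and every dosed subject enters the all-treated analysis. Part C efficacy is only listed by dose level, so the rate question concerns Part D.

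None of this removes the conflict over evaluability itself, which both documents state as a settled rule.

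**Conclusion.** The contradiction between Operations Manual 3.16 and Section 7.7 is real. It concerns AML subjects who stop in Cycle 1 through death or progression, or who stop for another reason but have a post-baseline assessment. It changes who counts toward the 20 response-evaluable subjects in Part D and the denominator to which Table 5 refers. It does not inflate the Part D rate if Sections 7.2 and 7.3 are followed. A rate based on the manual's definition would selectively lose early failures: with 24 treated, 5 responders and 2 to 6 such losses, it would be 22.7% to 27.8% instead of 20.8%, with lower bounds of 0.144 to 0.177 instead of 0.131. The loss counts and the responder count are assumptions. Efficacy is a preliminary secondary objective and the all-treated rule is explicit, so this is a moderate consistency correction and not a must-fix.

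**What to change.** In Operations Manual 3.16, replace the non-evaluability sentence, and align the preceding sentence that limits assessment to subjects completing a cycle. Suggested text:

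> Response evaluability for AML subjects is as defined in Protocol Section 7.7. Treated AML subjects without a post-baseline response assessment remain in the all-treated denominator and are counted as non-responders for CRc, CR + CRh and ORR.

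Deleting only the non-evaluability sentence would not be enough, because the preceding one would still tie assessment to completion of Cycle 1. The second sentence of the suggested text also settles how a Cycle 1 death is counted, which the resistant-disease definition leaves open.

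In Section 7.7, change first baseline assessment to first post-baseline response assessment.

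The cost is a few sentences, with no added procedures or subjects. The AML rate may be slightly lower than under the manual's rule. The change should be made before Part D outcomes are known.
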